## Abstract

A diagnosis of cancer impacts the person’s physical and mental health and the psychosocial and financial health of their caregivers. While data on the experience of living with cancer is available, there is a dearth of data from persons in low- and middle-income countries (LMICs). The perspectives of other impacted individuals also remain understudied (e.g., bereaved family members), as well as the impact on survivors and their families over time. The objective of this study is to describe the psychosocial and financial impact of cancer on people diagnosed with cancer as a child, adolescent or adult, their families/caregivers, and the family members of those who have died from cancer, in high-income countries (HICs) and LMICs. This study is an observational, descriptive, quantitative study. Data will be collected anonymously via a digital online cross-sectional survey distributed globally by the World Health Organization (WHO) via the LimeSurvey software. Participants will include (a) adults aged 18+ who have been diagnosed with cancer at any age, who are currently undergoing cancer treatment or who have completed cancer treatment; (b) adult family members of individuals of any age with a cancer diagnosis, who are currently undergoing cancer treatment or who have completed cancer treatment; and (c) bereaved family members. Participants will be anonymously recruited via convenience and snowball sampling through networks of organisations related to cancer. Survey results will be analysed quantitatively per respondent group, per time from diagnosis, per disease and country. Results will be disseminated in peer-reviewed journals and at scientific conferences; a summary of results will be available on the WHO website. This study will suggest public health interventions and policy responses to support people affected by cancer and may also lead to subsequent research focusing on the needs of people affected by cancer.

## Introduction

### Background

Cancer is a leading cause of illness and mortality. In 2020, nearly 20 million people developed cancer, and nearly 10 million deaths were caused by cancer [1]. Regardless of setting or context, a diagnosis of cancer marks the start of a long and complex journey for the person living with cancer and their family. This journey impacts not only the person’s physical health but also their mental health, as well as the psychosocial [2] and financial health of the family unit [3, 4].

Documenting the lived experience of people affected by cancer is the first step to identifying how services can be organised to meet their needs. This is an essential prerequisite to implementing integrated people-centred care which aims to put people and their communities at the centre of health systems [5]. The ‘lived experience of people affected by cancer’, or ‘lived cancer experience’, is defined here as the experience of living or having lived with cancer, including, but not limited to the experience of receiving treatment for cancer and/or supporting someone through cancer and beyond, in the long-term after treatment has finished.

The psychosocial dimensions of the impact of cancer can be organised into the following categories, which are themselves interlinked: psychological, social, and financial. These are described below.

#### Psychological impact of cancer

Mental health disorders such as adjustment, anxiety and depressive disorders, secondary to cancer treatment are commonly reported in review articles [2, 6, 7], A meta-analysis of 94 interview-based studies reported that a combination of mood disorders could occur in up to 30–40% of adults, in hospital oncological and palliative care settings, although the vast majority of these data are collected in HICs [7]. The psychosocial morbidity associated with cancer increases the burden of disease and is associated with a reduction in quality of life, poor adherence to treatment and possibly, decreased chances of survival [6, 7].

A systematic review of the prevalence of depression and anxiety among people at least 2 years after a cancer diagnosis, found that anxiety was more prevalent among cancer survivors (17.9%; 95% CI 12.8–23.6) compared to healthy controls (13.9%; 95% CI 9.8–18.5; with a RR of 1.27 (95% CI 1.08–1.50; p = 0.0039). This study also found that anxiety was common among spouses of cancer survivors, with a prevalence of anxiety in survivors of 28.0% (95% CI 22.3–33.9) and 40.1% among spouses (95% CI 25.4–55.9) [8]. Most participants from this study were from HICs.

Multiple studies have reported symptoms of depression, anxiety, post-traumatic stress disorder (PTSD), behavioural problems, and drug and alcohol misuse in survivors of childhood and adolescent cancer at higher rates than their peers [9–12]. In parents of childhood cancer survivors, two systematic reviews report that worry and disease-related thoughts, anxiety, PTSD and depression also occur more frequently than in controls, though again, data is predominately from HICs [13, 14]. Finally, a systematic review of studies in HICs comparing psychosocial functioning in siblings of childhood cancer survivors with their peers found significantly more symptoms of PTSD and poorer academic performance as well as greater likelihood to engage in risky health behaviours in adulthood [15], especially for those who report less social support [15].

The limited data from LMICs shows impaired health-related quality of life one year after diagnosis in 8 countries in Southeast Asia [16] and rates of depression and anxiety of up to 21% and 18% respectively in adults with cancer [17]. However, there remains a substantial lack of research in many LMICs in comparison to HICs, on the mental health outcomes of long-term survivors and of certain groups of people affected by cancer, such as children, and their family members. Even in HICs, certain vulnerable populations of cancer survivors and their families, such as rural and disadvantaged socioeconomic populations, experience high rates of anxiety, depression and distress [18] and an elevated and prolonged need for mental healthcare [19], yet their needs are yet to be explored on a global level.

Grief is an additional need and an anticipated response following a cancer diagnosis or death of a loved one. In certain situations, when the grieving process becomes prolonged, it may lead to prolonged grief disorder, which can itself contribute to significant challenges in psychosocial functioning [20–22]. Although bereaved parents of children with cancer demonstrate resilience, protracted grief reactions such as prolonged grief disorder [23] are associated with poor quality of life and psychological and physical health outcomes, including more mortality [22, 24–27]. A systematic review of studies from HICs examining the psychosocial outcomes of cancer-bereaved children and adolescents shows high levels of adjustment, though some studies did show frequent unresolved grief and a higher risk of self-harm in bereaved adolescents [28]. Most of the data examines response in the medium-term, but data in the long-term, particularly 10 or more years after death, is lacking.

Importantly, a cancer diagnosis and treatment can also result in positive psychological outcomes. Survivors and their families have, for example, reported increased resilience, post-traumatic growth, positive health behaviour changes, and increased benefit-finding after diagnosis and treatment [28–31].

#### Social outcomes

Cancer has an important impact on the social lives of people of all ages. Systematic reviews have reported that adults with cancer may experience social difficulties, such as loneliness and social isolation [32, 33], challenges in their marital/partner relationships [34, 35] and sexual dysfunction [36]. They may benefit from targeted psychosocial interventions to improve social function and quality of life, as demonstrated in a meta-analysis of 22 randomized controlled trials [37]. A systematic review examining the social and economic impact of cervical cancer on women and children in LMIC demonstrated mixed results in terms of social support and independence, with most qualitative studies reporting social isolation, strained relationships with their partners, and a negative impact on independence, but also in some quantitative studies, high levels of social support [38].

When it comes to adolescent and young adults (AYAs) with cancer, a systematic review of studies mostly in HICs shows that AYAs aged 15–39 can experience more problems in social functioning and have poorer social quality of life than their peers without cancer [39]. This includes problems with employment, with the maintenance and development of peer and family relationships, intimate and marital/partner relationships, and needing peer support, even years after diagnosis [39, 40]. A systematic review examining the determinants of social functioning among AYAs with cancer shows that adequate social support is associated with increased social functioning in this population [41]. Most of the data on child and adolescent cancer arise from HICs and do not extend into the long-term.

#### Financial toxicity

Financial toxicity and financial hardship are used interchangeably to describe the distress caused by the economic burden of cancer care [42, 43]. Nearly half of all people living with cancer experience a financial impact, which is more pronounced in people who lack health insurance, have a lower income, are unemployed, come from a minority ethnicity, or are younger at diagnosis [3, 44–46]. Financial toxicity is closely linked with financial distress and can lead to the decision to forego care [45]. Two systematic reviews [47, 48] studied financial toxicity in HICs with a publicly funded healthcare, one of them including qualitative studies only [48]. Direct material hardship and a reduction in financial resources is related to out-of-pocket expenses for medical care and indirect costs such as those associated with travel or housing during treatment, loss of income and assets and medical debts, with the majority of studies focusing on patients rather than caregivers [47, 48]. Survivors also face significant costs of long-term access to care for chronic conditions secondary to cancer treatment, as demonstrated in a survey of 1656 cancer survivors in the USA [49].

While there is limited data from studies conducted in LMICs, available data suggests a very significant financial impact, with many families reporting a need to ask for money from charity, borrow money, or sell possessions to access healthcare [50, 51]. A longitudinal study of 9513 adults with cancer in Southeast Asia found that economic hardship was reported by up to a third of families and that 48% of adults had experienced financial catastrophe 12 months after diagnosis (defined as out-of-pocket costs equal to or exceeding 30% of annual household income). The risk was increased in people of low income groups and in those without insurance or whose insurance does not cover the costs of treating cancer [52, 53]. In LMICs, the economic impact of cervical cancer on women affected has been reported as a decline in the standard of living, a need to rely on family members as well as loss of hours of employment. However, the indirect costs of cancer and the broader effects on family are yet to be better described [38].

Productivity loss is another factor contributing to economic hardship, which extends into survivorship [49]. Productivity loss results from lost employment, prolonged leaves of absence due to medical appointments and hospitalizations, and an inability to participate in work-related activities or to re-enter the workforce after treatment, contributing to financial toxicity [4, 45, 46, 48]. A study conducted in the BRICS countries (Brazil, Russia, India, China, and South Africa) estimated the lost productivity due to premature cancer mortality in 2012 to reach 46.3 billion US dollars, with the largest total productivity loss seen in China [54]. This study was completed over a decade ago, and given the increased global cancer prevalence, ageing and growth of the population [55], this loss is likely to be significantly higher today.

For survivors of childhood and adolescent cancer, studies from HICs suggest that they are less likely to graduate from university, be employed, or live independently compared with peers or siblings without a cancer history [56–60]. They have also reported to have lower wages and require social security for income supplementation [61]. Australian data suggests that the lifetime productivity loss of AYAs aged 15–25 years diagnosed with cancer in 2016 will be $508.4 million AUD. These costs result from productivity losses associated with absenteeism from school, lower workforce participation, premature mortality, informal carer costs and administrative costs [62]. Data from the USA suggests costs from productivity losses of AYAs aged 15–39 years diagnosed with cancer total $18.3 billion USD [63].

Many families of a child with cancer must manage the direct and indirect costs of treatment whilst simultaneously needing to reduce their working hours to care for their child. Effects on income losses can be ongoing, for years after treatment ends. Families of low socioeconomic background, mothers who were on maternity leave at the time of their child’s diagnosis, and single mothers are at greatest risk of employment loss [64–66]. Adult siblings of childhood cancer survivors in the United States are also more likely to suffer diverse forms of financial hardship such as difficulty paying bills or foregoing medical care, than the general population [67]. Importantly, in a systematic review of the socio-economic impact of childhood cancer on parents, only 6 of the 29 studies were from LMICs in Asia and Africa, further highlighting the lack of data available in LMICs [66].

Finally, financial hardship due to cancer increases the risk of psychological consequences, such as social isolation and elevated stress and worry, [45, 47, 48, 64] across the lifespan and is associated with lower health-related quality of life [68]. Assessing risk for financial hardship from the time of diagnosis throughout the cancer trajectory is an evidence-based standard for psychosocial care of children and adolescents with cancer [69].

### Rationale

Overall, the effects of cancer are broad. However, data on the lived cancer experience from LMICs, and data comparing psychosocial effects to those experienced by people in HICs, particularly in the long-term after cancer treatment, is lacking. This is particularly important given there are likely fewer psychosocial and financial supports available for people with cancer in LMICs.

Understanding the immediate and long-term lived cancer experience of people on a global level, particularly in areas of unmet need, would allow identification of key targets for health systems and policy intervention. Strengths and novelties of this study include its global nature, its availability in different languages and the fact that it targets individuals and family members during and after cancer treatment.

## Material and methods

### Aims

The aims of the study are to understand and describe the immediate and long-term psychosocial and financial impact of cancer on people diagnosed with cancer as children and as adults, their families/caregivers and the family members of those who have died from cancer in HICs and LMICs.

### Design

This study is an observational, descriptive, quantitative, cross-sectional study with some open-ended questions, distributed by the World Health Organization (WHO) Headquarters amongst all member countries and regions [70].

### Governance

The study was designed by a 9-member Steering Committee representing people with lived experience of cancer (survivors and parents), professional disciplines (oncology, psychology, social work, statistics, research, clinical trials), organisations (WHO, community organisations, universities, hospitals) and regions (US, Europe, Africa, Australia). Throughout the course of the project, the Committee met monthly via videoconference, finalising study aims, developing the study design, drafting the study protocol and survey questionnaire, and contributing to project management. The Committee is also responsible for collecting stakeholders’ and initial participants’ feedback and finalising the survey questionnaire. The Committee will advise on policy impacts of the project and ensure that translation and sustainability are at the forefront of planning. The Committee will disseminate newsletters and annual reports to all stakeholders. Following project launch, the Committee will invite additional members as needed, including, for example, underrepresented groups of people with lived experience (e.g., fathers, culturally diverse people, First Nations people) through direct contact with cancer organisations and institutions prior to re-launch, to ensure that the project is culturally safe and inclusive. We will continue to invite additional professional experts as needed (Fig 1).

**Fig 1 pone.0294492.g001:**
[figure not shown]
Project governance.

The Steering Committee is supported by a larger Advisory Panel, comprising up to 50 stakeholders who provided feedback on survey questionnaire content and length, participate in study webinars, and promote the study to their networks, amongst other activities. Advisory Panel members include people with lived experience of cancer, representatives from relevant cancer community organisations around the world, WHO staff in regional offices, members of the Global Childhood Cancer Initiative [71], and other individuals as relevant. The study is supported by additional experts and consultants (e.g., graphic design, communications, translation services) as needed.

### Measures

The survey questionnaire was developed by the Steering Committee utilising the WHO Quality of Life framework, with additional questions included from a series of validated tools. The research team also purposely developed additional items where validated items were not available. Some open-ended questions were added to elicit valuable insights and to capture the voices of survivors and family members, particularly on issues the survey questionnaire may have missed. The content of the survey questionnaire was shared with the Advisory Panel engaged in this project to ensure that important medical, psychosocial, and financial aspects were included to ensure cultural sensitivity. A summary of the structure and content of the survey questionnaire, with a list of the different topics addressed, the items included, the measure and response options, and the participants to whom each item is directed is provided (Table 1; comprehensive S1 Table). The comprehensive table is available as supplementary material.

**Table 1 pone.0294492.t001:** Summary of items in survey questionnaire. Aims, measures and target participants.

Aim	Measure and response option	All People affected by cancer	Survivors	Family members of people affected by cancer	Bereaved family members
**Introductory questions**	Forced choice options. Items purposely developed.	**X**	**X**	**X**	**X**
**Demographics**	Mixture of forced choice options with options to add free text (e.g., ‘other’), depending on the question. Items either purposely developed or based on Childhood Cancer Survivor Study or the FOCUS study.	**X**	**X**	**About self**	**About self**
**Clinical information about person with cancer**	Mixture of forced choice options with options to add free text (e.g., ‘other’). Items based on the FOCUS study.	**X**	**X**	**About their family member (excluding type of treatments received)**	**About their family member (excluding types of treatment received)**
**Survivorship care experiences**	Items based on the FOCUS study	**X**	**X**	**-**	**-**
**Fertility experiences of person with cancer**	Mixture of forced choice options with options to add free text (e.g., ‘other’). Items purposely developed.	**X**		**-**	**-**
**Perceived impact of cancer**	Items based on the FOCUS study	**X**	**X**	**-**	**-**
**Impact on marriage/ relationship (if applicable)**	Purposely developed	**X**	**X**	**X**	**X**
**Education/work problems**	Adapted from Long Term Follow Up study questionnaire and purposely developed	**-**	**X**	**X**	**X**
**Caregiver burden**	Family Appraisal of Caregiving Questionnaire for Palliative Care (FACQ-PC) by Cooper et al. 2006 [75], and an additional item purposely developed			**Self**	**Self**
**Prolonged Grief**	Prolonged Grief Scale by Prigerson et al. 2021 [76]	**-**		**-**	**Self**
**Impact of cancer on siblings**	Sibling Cancer Needs Inventory (Patterson et al. 2014) [77] and purpose-designed questions (11 items)	**-**		**Siblings only**	**-**
**Health-related quality of life**	PROMIS Global	**X**		**Self**	**Self**
**Health behaviours**	Purposely developed	**X**	**X**	**Self**	**Self**
**Emotional problems**	Purposely developed	**X**	**X**	**Self**	**Self**
**Mental health**	Purposely developed	**X**	**X**	**Self**	**Self**
	Items based on the FOCUS study	**X**	**X**	**Self**	**Self**
	PROMIS Anxiety short form	**X**	**X**	**Self**	**Self**
	PROMIS Depression short form	**X**	**X**	**Self**	**Self**
**Financial well-being**	Purposely developed	**X**	**X**	**Self**	**Self**
	COST measure developed by De Souza et al 2017 [78]	**-**	**X**	**Self**	**Self**
	COST Measure, developed by De Souza et al 2017 [78]	**X**		**Self**	**Self**
**Support service use**	Based on a National Cancer Institute Survey	**X**	**X**	**Self**	**Self**
**End of life care experience**	Purposely developed	**-**	**-**	**-**	**Self and family member**
**Post-traumatic growth**	Purposely developed	**X**		**Self**	**Self**
**Missed topics**	Purposely developed	**X**		**Self**	**Self**

### Ethics and safety considerations

Ethics approval was obtained through the WHO Ethics Review Committee (ERC). This study was deemed exempt from formal review by the Committee, given its low-risk nature. The survey questions are designed for general use across HICs and LMICs, so no ethical approval will be sought from individual participating countries.

The Steering Committee considered the priorities and needs of populations in low resource settings, as outlined in the Council for International Organizations of Medical Sciences (CIOMS) Ethical guidelines on Research conducted in low-resource settings [72], the principles of which are met in this study. Electronic consent is included within the online survey.

### Participants and recruitment

Four groups of participants will be recruited:

i)Adults currently living with cancer (with a cancer diagnosis or undergoing cancer treatment)ii)Survivors of childhood, adolescent, or adult cancer, who have completed cancer treatmentiii)Family members or caregivers of people with cancer or long-term survivorsiv)Bereaved family members or caregivers who have lost a family member to cancer.

The inclusion criteria is defined as an individual who:

Is an adult older than or equal to 18 years of age andHas had a cancer diagnosis (in childhood or adulthood): this includes adults who are currently undergoing treatment, and who have finished treatment or are not currently receiving treatment (including survivors of childhood, adolescent, young adult or adult cancer).

Or as an individual who:

Is 18 years of age or older andIs a family member (spouse, child, sibling, or other primary caregiver) of a person ever diagnosed with cancer orA family member (spouse, child, sibling, or other primary caregiver) of a person who has died from cancer

The exclusion criteria are defined as:

Children under 18 years of age. These children will be represented by their parent or guardian.Siblings under 18 years of age of a person with a cancer diagnosis.

Non-English speaking people will be invited to participate. The survey questionnaire will be translated in the five other United Nations languages (Spanish, French, Chinese, Russian, Arabic) through the WHO Headquarters Interpretation services. Other languages may also be represented depending on availability of translators. After translation, the survey questionnaire will be reviewed by native speakers amongst the study team, where possible, to ensure that translations are adapted to culture, context, and use of language. The survey questionnaire will be reviewed within WHO by a staff member with Health Literacy expertise to ensure the content is adequate for health resource-constrained countries.

Participants will be anonymously recruited via convenience and snowball sampling through networks of organisations related to cancer. To date, the survey has been shared within the WHO and with partner networks of international cancer organisations via a webinar, direct meetings, as well as through direct emails to organisation leaders. Cancer organisations that were chosen to disseminate the survey focus on childhood and on adult cancer (including specific cancers such as women’s cancer), with a broad geographical representation. These include professional partner organisations, research institutes, as well as foundations and advocacy groups (S2 Table). Organisations will be permitted to advertise the survey on social media a maximum of three times. Physicians and other healthcare providers have not directly been approached to identify participants.

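### The stated translation route covers the validated scales and includes no described check of score equivalence, so HIC/LMIC contrasts in scale scores may partly reflect language version

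*Protocol article*

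**What the plan says.** Under *Participants and recruitment*, the protocol article gives one translation route: "The survey questionnaire will be translated in the five other United Nations languages (Spanish, French, Chinese, Russian, Arabic) through the WHO Headquarters Interpretation services". Beyond those five, "Other languages may also be represented depending on availability of translators". The check on the result is conditional: "After translation, the survey questionnaire will be reviewed by native speakers amongst the study team, where possible". The aim given for that check is fit to culture, context and usage. A further sentence adds: "The survey questionnaire will be reviewed within WHO by a staff member with Health Literacy expertise".

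Under *Measures*, the questionnaire is described as built on a WHO quality-of-life framework, "with additional questions included from a series of validated tools". Table 1 names them: PROMIS Global, the "PROMIS Anxiety short form" and its depression counterpart, COST, the caregiving questionnaire (FACQ-PC), the Prolonged Grief Scale and the Sibling Cancer Needs Inventory. Many other items were written for this survey. *Measures* also reports that the Advisory Panel saw the content, partly for cultural sensitivity. *Timeline and status* reports a pilot in three languages: English, French and Spanish.

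*Aims* and *Study outcomes* both call for description in HICs and LMICs. *Rationale* says the literature lacks "data comparing psychosocial effects to those experienced by people in HICs". *Data analysis* lists respondent group, time from diagnosis, disease and age group, and country as breakdowns. Its limitations cover selection, non-response and the heterogeneity of participants.

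**The concern.** Once a scored scale is translated afresh, its items may be easier or harder to endorse than in the validated version, and the mean score may move with them. A review that adapts wording to local usage suits items written for this survey. For a scored scale it does not show that the score level is preserved, and adaptation may itself change that level.

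This matters because the study sets out to describe HICs and LMICs on these scales, and the results are meant to feed a WHO practice brief with recommendations for Member States. If one income group answers translated versions more often than the other, a version shift enters the contrast between them. A larger sample makes such a shift more precise; it does not remove it. The matter is also time-bound: responses are anonymous and there is no follow-up unless a participant volunteers contact details, so wording cannot be repaired after collection.

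**Working it through.** **1. The plan's own precision figures.** Inputs from *Data analysis*: n = 300 per subgroup, 95% confidence.

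- Mean: 1.96/√300 = 0.113 SD. Stated: ±0.11 SD.
- Proportion at p = 0.5: 1.96 × √(0.25/300) = 0.0566, or 5.7%. Stated: no larger than ±6%.

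Both reproduce. No stated figure is in dispute.

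**2. The right yardstick for a contrast.** The 0.11 SD margin is for one group's mean. For a difference between two independent groups of 300:

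- SE = √(2/300) = 0.0816 SD
- 95% margin = 1.96 × 0.0816 = 0.160 SD

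If the anticipated 2000 respondents split evenly by income level (an assumption), the margin is 1.96 × √(2/1000) = 0.088 SD.

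**3. How a version shift enters.** Let p be the share of an income group answering a translated version, and d the shift of that version from English, in SD, taken as common to all translations. With no true difference,

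spurious difference = (p in LMICs − p in HICs) × d.

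The documents give neither p nor d. Assume p = 0.70 in LMICs and 0.30 in HICs:

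| Assumed d (SD) | 0.40 × d (SD) | Against 0.160 SD (300 per group) | Against 0.088 SD (1000 per group) |
|---|---|---|---|
| 0.2 | 0.08 | inside | inside |
| 0.3 | 0.12 | inside | outside |
| 0.5 | 0.20 | outside | outside |

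**4. How often it would mislead.** With 300 per group, a net shift s and no true difference, the probability that the 95% interval for the difference excludes zero is

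1 − Φ(1.96 − s/0.0816) + Φ(−1.96 − s/0.0816).

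| Net shift s (SD) | Probability |
|---|---|
| 0 | 5% |
| 0.05 | 9% |
| 0.10 | 23% |
| 0.20 | 69% |
| 0.30 | 96% |

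**5. Do the stated safeguards test score equivalence?**

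- Native-speaker review: conditional, and directed at adaptation of wording.
- Health-literacy review: directed at suitability of content for resource-constrained countries.
- Advisory Panel: directed at coverage of content and cultural sensitivity.
- Pilot: English, French and Spanish only, with LMIC respondents under-represented by the article's own account. Chinese, Russian and Arabic were not included.

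None is described as comparing scores between language versions.

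**The case against.** The strongest reply is that the article never says in so many words that the validated scales are translated afresh. The comprehensive item table and the full protocol are not shown, and they may specify existing language versions. This stands in part. Coverage of the scales is the plain reading of a route stated for the whole questionnaire, but it is still a reading. The request should therefore be to state which version is used, and should not assert that validated versions are ignored.

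A reader might also infer that the conditional review, "reviewed by native speakers amongst the study team, where possible", is the only check. It is not, since a health-literacy review, Advisory Panel input and a pilot are also reported. What stands is that none is described as checking score equivalence.

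The size is open to challenge as well. The link between language and income level, the 70%/30% split and the common shift are all assumed. Shifts in different languages could partly cancel, and a smaller gap in language mix dilutes the effect in proportion. Against a 0.160 SD margin, only the largest illustrated case falls outside.

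Finally, the study is descriptive, names no HIC/LMIC test and disclaims causal conclusions. That limits the harm without removing it, because a shifted descriptive contrast can still be read as a difference in need.

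**Conclusion.** The concern holds as a cheap improvement to a stated method. The article fixes one translation route for a questionnaire that contains scored scales and describes no step that would show whether scores are comparable between versions. If the language mix differs by income level, HIC/LMIC contrasts on those scales may carry a version shift.

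The size cannot be derived from the documents. The illustration of 0.08 to 0.20 SD rests on an assumed 70%/30% split and an assumed common shift of 0.2 to 0.5 SD, and should be read against 0.160 SD for two groups of 300, not the one-group 0.11 SD.

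A reader might go further and infer that any HIC/LMIC difference would be impossible to tell from a translation artefact. The documents do not support that. Language varies within income groups to an unknown degree, nothing in the plan prevents survey language from being recorded, and contrasts within one language hold the version fixed.

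**What to change.** 1. For each named validated scale, use the developer's existing language version where there is one. If this is already done, one sentence saying so settles this part. Keep the WHO translation route for the purposely developed items, and for scales or languages without an existing version.
2. Record the survey language of each response. For scale-based HIC/LMIC descriptions, add summaries with 95% confidence intervals within each language that has respondents in both income groups, labelled as a sensitivity description. List language version among the limitations of HIC/LMIC contrasts.

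Do not add a rule that accepts a difference only if its direction is the same in every language. Such a rule ignores precision and says nothing about a language found in only one income group. It can also suppress real differences. Assume 50 respondents per income group in each of four languages and a true difference of 0.15 SD: the SE is √(2/50) = 0.20 SD, each language shows the right direction with probability Φ(0.75) = 0.77, and all four agree with probability 0.77⁴, about 0.36 (reading the four languages as independent).

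The cost is permission for existing versions, where needed, and one extra set of tables. Within-language cells will be smaller: at 50 per group the margin for a difference is 1.96 × 0.20 = 0.39 SD. Part 1, and the recording of language in part 2, must be in place before collection on the final survey.
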